**Methods/Design:**

This is a prospective observational study. We anticipate collecting data on over 5000 critically ill children admitted to 31 pediatric intensive care units (PICUs) across the world during the calendar year of 2014. Data will be collected for seven days on all children older than 90 days and younger than 25 years without baseline stage 5 chronic kidney disease, chronic renal replacement therapy, and outside of 90 days of a kidney transplant or from surgical correction of congenital heart disease. Data to be collected includes demographic information, admission diagnoses and co-morbidities, and details on fluid and vasoactive resuscitation used. The renal angina index will be calculated integrating risk factors and early changes in serum creatinine and fluid overload. On days 2–7, all hemodynamic and pertinent laboratory values will be captured focusing on AKI pertinent values. Daily calculated values will include % fluid overload, fluid corrected creatinine, and KDIGO AKI stage. Urine will be captured twice daily for biomarker analysis on Days 0–3 of admission. Biomarkers to be measured include neutrophil gelatinase lipocalin (NGAL), kidney injury molecule-1 (KIM-1), liver-type fatty acid binding protein (l-FABP), and interleukin-18 (IL-18). The primary outcome to be quantified is incidence rate of severe AKI on Day 3 (Day 3 – AKI). Prediction of Day 3 – AKI by the RAI and after incorporation of biomarkers with RAI will be analyzed.

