### Exclusion criteria

Maintenance hemodyialysis or peritoneal dialysis.Chronic kidney disease with a baseline estimated glomerular filtration rate (eGFR) of < 15 ml/min/1.73 m^2^.Kidney transplant within 90 days of PICU/CICU admission.Post-operative from surgical correction of cyanotic congenital heart disease within 90 days of PICU/CICU admission.Uncorrected congenital heart disease (does NOT include patients with an isolated atrial or ventricular septal defect, patent ductus arteriosus, or patent foramen ovale).Immediately following elective cardiac catheterization.

For exclusion criteria 4–6, patients admitted and then taken to the operating theater for surgical corrections requiring cardiopulmonary bypass are included for study.

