### Variable collection

Data collected per patient encompasses admission demographic data, daily morning hemodynamic parameters, daily laboratory values specific for kidney function, assessments of fluid balance including net fluid in and net fluid out, and use of nephrotoxins or diuretic agents. For admission epidemiology, primary ICU diagnoses are broadly divided into shock/infection/major trauma, medical cardiac, respiratory failure, post-surgical/minor trauma, central nervous system dysfunction, and pain/sedation management. Net fluid balance is divided into total fluids and urine flow rates derived per kilogram admission body weight per hour. Daily calculated values include:Estimated change in creatinine clearanceCalculated as percent change of daily creatinine from baseline creatinine.Baseline creatinine used is lowest consistent serum creatinine 90 days or more prior to admission.For patients without a prior baseline, an assumed creatinine clearance of 120 ml/min/1.73 m^2^ is used [3].Percent fluid overloadCalculated as previously described [31].Fluid corrected serum creatinineCalculated as previously described [32].KDIGO stage AKI by creatinineBased on KDIGO AKI guidelines [33].

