### Renal angina index calculation

To ascertain fulfillment or absence of renal angina on the day of admission, the renal angina index will be calculated as previously described (Additional file 2) [5]. An RAI of ≥8 will be interpreted as fulfillment of renal angina.

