### Primary and secondary outcomes

Our primary outcome is to report the epidemiology and associated outcomes of pediatric AKI worldwide (in over 30 PICUs, 12 different countries, 5 continents). This outcome is dependent on broad enrollment from participating centers. AKI is defined as KDIGO stage 2 or 3 AKI by creatinine and/or urine output criteria on Day 3 or later of PICU/CICU admission (Day 3 AKI).

Our secondary outcomes are to validate and refine the renal angina risk stratification model for prediction of Day 3 AKI.Determine if fulfillment of renal angina on Day 0 is predictive of severe AKI on Day 3 of PICU/CICU admission across the heterogeneous patient landscape of our participating centers. The AWARE data repository will be used to validate the precision of the RAI in ruling out AKI.Determine if prediction of Day 3 AKI by an RAI ≥ 8 is augmented by inclusion of urinary biomarkers alone or in combination.

Longer term outcomes to be followed include duration of mechanical ventilation, use of continuous renal replacement therapy, use of extracorporeal assist devices such as extracorporeal membrane oxygenation (ECMO) or ventricular assist devices (VADs), ICU length of stay, and mortality (Day 30 follow up).

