The design of this prospective study has limitations. We make several assumptions with regards to the expected incidence of AKI per PICU/CICU center. Differing geographic areas included in our enrollment study list and different patient demographics may have greater or less incidence of AKI risk. Many pediatric patients have no ‘baseline’ creatinine measured prior to the time of acute illness. Our assumption of a normal creatinine clearance is based on the use of this paradigm in previous study [4]. Additionally, we assume that 33% or greater of our enrollment sites will be able to capture urine for the biomarker analysis. Perhaps the greatest limitation is that this study is being independent of financial reimbursement. Study coordinators, research coordinators, and data management specialists at each site are not compensated for the exclusive purpose of this study, which has the potential to bias the enrollment strength of each center (depending on staff enthusiasm and availability). All of these limitations can also be interpreted as strengths of the study, however. Our initial results indicate that the AWARE study will assemble a broad and heterogeneous patient repository and that the pro bono work done by our coordinating sites is robust. It is our expectation that the AWARE study will serve as a model, a proof of concept that resources are in place to facilitate broad based pediatric AKI studies, for future large scale multicenter studies that are funded and sponsored by governmental and private financial support.

AKI is a significant disease syndrome affecting a large proportion of pediatric ICU patients. Existing data indicates that patients are not just dying with AKI, but *from* AKI [35]. AWARE is a first of its kind and vital study of critically ill children that will inform the pediatric critical care nephrology community of the prevalence and associations of AKI across the globe, offering new perspectives for prediction and detection of disease.

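### In children with no prior creatinine, one assumed clearance of 120 appears to underlie both the Day 0 RAI and the Day 3 AKI outcome, so RAI accuracy can be overstated and biomarker accuracy understated relative to it

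*Protocol article*

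**What the plan says.** Variable collection gives a two-step rule for baseline. If a prior value exists, "Baseline creatinine used is lowest consistent serum creatinine 90 days or more prior to admission". If not, "For patients without a prior baseline, an assumed creatinine clearance of 120 ml/min" per 1.73 m² applies. The rule sits under the daily change in creatinine clearance. KDIGO stage by creatinine follows in the same list of daily values, with no baseline of its own.

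The predictor is described in the Abstract: "The renal angina index will be calculated integrating risk factors and early changes in serum creatinine and fluid overload". Under Renal angina index calculation, "An RAI of ≥8 will be interpreted as fulfillment of renal angina", and the formula is left to Additional file 2, which is not shown.

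The outcome is set under Primary and secondary outcomes: "AKI is defined as KDIGO stage 2 or 3 AKI by creatinine and/or urine output criteria on Day 3 or later" of the ICU stay. The secondary aims ask whether the Day 0 RAI predicts this outcome and whether urinary biomarkers improve that prediction. The Analysis section adds NRI and IDI for comparing discrimination.

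The Discussion acknowledges that many children have no measured baseline and defends the rule by precedent: "Our assumption of a normal creatinine clearance is based on the use of this paradigm in previous study". On chronic kidney disease, the Exclusion criteria remove only "Chronic kidney disease with a baseline estimated glomerular filtration rate (eGFR) of < 15" ml/min/1.73 m², besides maintenance dialysis and recent kidney transplant.

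**The concern.** An assumed baseline is an ordinary compromise when no prior value exists. The difficulty is that the same assumed value appears to be used twice. In a child without a prior creatinine, an error in the 120 raises or lowers the apparent Day 0 creatinine change and the apparent Day 3 stage together, even if kidney function never changes. Predictor and outcome then agree partly because they share an error.

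The urinary markers are assayed directly and use no baseline, so they cannot follow the erroneous part of the outcome. The secondary aims set marker performance beside the RAI, and for this group the reference outcome is tilted towards the RAI. The Discussion discloses that normal clearance is assumed but not that the error is shared.

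**Working it through.** **The plan's own figures.** The plan states no AUC, effect size or power for the RAI or the markers, so no stated figure depends on the baseline rule. Its sample sizes reproduce: 150 × 35 = 5,250, and 5,250 / 3 = 1,750 with urine.

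**Step 1: the shared factor.** Assume that steady-state creatinine is inversely proportional to clearance. With no acute change, the apparent ratio on every day is 120 / true clearance:

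- 120 / 100 = 1.2
- 120 / 80 = 1.5
- 120 / 60 = 2.0
- 120 / 40 = 3.0
- 120 / 150 = 0.8

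Taking a ratio of 2 as the stage 2 threshold (an assumption; the document cites the guideline without restating it), a stable child at 60 or below without a prior value is recorded as severe AKI on Day 0 and on Day 3. Such a child is eligible.

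**Step 2: the mechanism alone.** Simulate no acute AKI in anyone, 50% on the assumed value, CV of true clearance 25%. Recorded AKI is 0.2% (median 120) to 1.3% (median 100), all false. An RAI-type score predicts it with AUC 0.97 to 0.99; the marker's AUC is 0.49 to 0.50. This shows how the error works and is not an estimate of size.

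**Step 3: with real AKI.** 200,000 children per scenario. In children without a baseline, log(120 / true clearance) is added to both the Day 0 and the Day 3 log ratio. The marker depends on true injury only, and the RAI is treated as a continuous score. True creatinine AKI is 12.6%, and 50% are on the assumed value. The medians, CVs and shares are assumptions.

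| Median, CV | False share of recorded AKI | True AKI missed | RAI AUC, recorded | RAI AUC, true | Marker AUC, recorded | Added AUC | IDI |
|---|---|---|---|---|---|---|---|
| All baselines measured | 0% | 0% | 0.851 | 0.851 | 0.802 | 0.032 | 0.060 |
| 140, 10% | 0% | 17% | 0.865 | 0.836 | 0.805 | 0.030 | 0.058 |
| 120, 25% | 19% | 10% | 0.859 | 0.814 | 0.774 | 0.026 | 0.056 |
| 100, 10% | 26% | 0% | 0.836 | 0.831 | 0.774 | 0.031 | 0.062 |
| 100, 25% | 34% | 3% | 0.854 | 0.804 | 0.742 | 0.021 | 0.048 |
| 80, 25% | 53% | 1% | 0.861 | 0.771 | 0.693 | 0.012 | 0.030 |

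With 10% urine-output AKI added (measured-baseline values: RAI 0.812, marker 0.777, added AUC 0.037, IDI 0.061):

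- Median 100, CV 25%: RAI 0.817 recorded, 0.768 true; marker 0.740; added AUC 0.030; IDI 0.057.
- Median 120, CV 25%: RAI 0.809 recorded, 0.777 true; marker 0.761; added AUC 0.037; IDI 0.065.

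**Step 4: a simpler model.** The predictor is the Day 0 creatinine ratio alone, with 10% true AKI, a true Day 3 ratio of 2.6, a marker effect of 1 SD, and 50% assumed. With measured baselines the creatinine AUC is 0.70, the marker AUC 0.76 and the marker's added AUC 0.11. At median 100:

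- CV 10%: creatinine 0.65, marker 0.76, added AUC 0.14.
- CV 25%: creatinine 0.68, marker 0.73, added AUC 0.11.
- CV 35%: creatinine 0.75, marker 0.69, added AUC 0.075, so the ranking reverses.
- CV 35% with 5% urine-output AKI: 0.69 and 0.71, no reversal.

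**The case against.** The strongest reply is that baseline error also adds noise to the predictor, and this can offset the shared-error effect. That stands. At median 100 and CV 10% the recorded RAI AUC is 0.836, below the 0.851 of a fully measured cohort, and the creatinine-only AUC falls from 0.70 to 0.65. A reader might infer that the RAI is always inflated, or that the ranking of RAI and biomarkers will reverse. Neither is general: the reversal needs a wide spread of clearance, and 5% urine-output AKI removed it.

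A reader might also infer that the added-value aim is biased against the biomarkers. The calculations do not support that as a rule. IDI fell in most cases but rose in two (0.060 to 0.062 and 0.061 to 0.065), and added AUC ranged from a fall to a rise.

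The simulations do not use the real RAI, whose formula is not shown and which also includes risk factors and fluid overload with a cut at 8. These parts dilute the effect. Children with known chronic kidney disease will often have a prior creatinine, so the example at 60 or 40 may concern few children; the documents give no count.

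Finally, the Analysis section pools sites and is silent on baseline source. It does not say that measured and assumed baselines are analysed together, and an analysis by source may stand in a fuller plan. What remains is that the article fixes the 120 rule, gives no alternative baseline, and does not state the shared-error consequence.

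**Conclusion.** The point holds in a conditional form. Given that the RAI and the KDIGO creatinine stage both use the stated baseline (inferred, with no competing definition in the document), their errors are shared in children without a prior value, and the urinary markers are outside that error.

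The firmest result is the gap between recorded and true performance. In every scenario of the Step 3 model with assumed baselines and real AKI, the RAI's AUC was higher against recorded AKI than against true AKI. In the cases shown the gap runs from 0.836 − 0.831 = 0.005 to 0.861 − 0.771 = 0.090. Marker AUC against recorded AKI was usually lower than against true AKI, but not when clearance was mostly above 120 (0.805 against 0.802). In that case the shared error hides AKI instead of creating it.

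The effect on added value runs from negligible or slightly favourable to the markers at CV 10% to a reversal of ranking at CV 35% with median 100 and no urine-output AKI. The documents do not allow a choice within that range.

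**What to change.** Keep the whole-cohort analysis. Record for each child whether the baseline was measured or assumed, and pre-specify RAI accuracy, biomarker accuracy and NRI/IDI separately for the two groups.

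In the assumed-baseline group, add a sensitivity analysis with a Day 3 outcome that does not use 120: the urine-output stage, or Day 3 creatinine relative to the child's own lowest in-stay value. Interpret any conclusion about RAI versus biomarkers according to whether it holds in both groups. State in the limitations that predictor and outcome share the assumed value.

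This needs wording and one flag; urine flow and daily laboratory values are already collected. The costs are these:

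- The strata are smaller. If half the children lack a baseline (assumption), the 1,750 with urine split into 1,750 × 0.5 = 875 each; at 25% the smaller group is about 438.
- Children with a creatinine from at least 90 days earlier may be selected for prior illness, so they should not become the sole reference result.
- An in-stay minimum can miss AKI already present on admission.
- The RAI's AUC may look less favourable.

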### Analysis

Analysis of data will be performed independently based on each specific aim.Data for the primary objective of describing the epidemiology of AKI will be presented as a descriptive model. The prevalence on day 0 and incidence of AKI in up to 7 days of ICU admission using KDIGO classification will be calculated for each site cohort to identify the geographical “hot spots” of pediatric AKI. The data then will be pooled into a single cohort to study the outcome of AKI. The whole cohort will be stratified on Day 3 into four sub-populations with: no AKI, AKI-KDIGO Stage 1, AKI-KDIGO Stage 2, and AKI-KDIGO Stage 3. An adjusted and unadjusted survival analysis models using log rank test and cox regression models will be used to compare the mortality rates and the need of renal replacement therapy between the 4 groups.The prognostic value of the renal angina index will be calculated on Day 0 for the development of Day 3 AKI. RAI will be evaluated as a diagnostic test and sensitivity, specificity, positive predictive value, negative predictive value, likelihood ratios, and receiver operating characteristics (ROCs) will be derived.Individual prognostic values of each of the four urinary biomarkers al one for Day 3 AKI will be calculated. The biomarkers will be tested in combination for changes in prognostic parameters and comparisons of discrimination using net reclassification improvement (NRI) and integrated discrimination improvement (IDI) will be derived. Finally, the contribution of each biomarker to the predictive model of renal angina for Day 3 AKI will be analyzed by integrating the biomarkers alone and in combination with the RAI.

Additionally, the association of renal angina index, urinary biomarker levels with clinical outcomes, including mortality, PICU length of stay, hospital length of stay, and renal replacement therapy provision, will be assessed using Chi-square test (or Fisher’s exact test for small counts) or Pearson correlation coefficient (or non-parametric Spearman correlation coefficient) based on the nature of data. Classification and regression tree analysis will be used to determine optimal decision rules for biomarker incorporation with RAI when discriminating for Day 3 AKI. In all analyses, a p-value of <0.05 will be considered statistically significant.

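### Crude site AKI rates are compared to find hot spots while children are staged from either a measured or an assumed baseline creatinine, so differences in baseline availability can pass for differences in disease.

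*Protocol article*

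**What the plan says.** **Two baselines.** The Variable collection section of the protocol article gives the first rule: "Baseline creatinine used is lowest consistent serum creatinine 90 days or more prior to admission". The second covers everyone else: "For patients without a prior baseline, an assumed creatinine clearance of 120 ml/min/1.73 m^2^ is used". Both stand under the daily percent change in creatinine. KDIGO stage by creatinine is a separate item in the same list, with a reference to the guideline. The natural reading is that the same baseline feeds that stage, though the article does not say so outright.

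**Site comparison.** Under the primary objective, the Analysis section says that prevalence on day 0 and incidence over up to seven ICU days "using KDIGO classification will be calculated for each site cohort to identify the geographical" hot spots. No standardisation, stratification or sensitivity analysis by baseline source is attached to this.

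**What is conceded.** The limitations in the Discussion say: "Many pediatric patients have no ‘baseline’ creatinine measured prior to the time of acute illness". They add: "Our assumption of a normal creatinine clearance is based on the use of this paradigm in previous study". They also say that AKI incidence may differ by region and demographics. They do not connect the assumed baseline with the comparison of sites.

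**The concern.** A child's creatinine stage is a ratio to baseline, and the two rules for that baseline err differently. The assumed value is wrong by whatever separates the child's true clearance from 120. A measured value does not carry that error. A site's crude rate therefore depends on its mix of the two rules.

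The mix is unlikely to be constant over PICUs in 12 countries, because it depends on earlier health-care contact and access to records. It also depends on age: children enter from 90 days of age, but a usable baseline must be at least 90 days old, so the youngest infants can hardly have one.

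At stake is which sites are called hot or cold spots. The error is systematic, so enrolling more children per site would not remove it, and it would act even if every site tested creatinine identically during the ICU stay.

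**Working it through.** **Plan's own figure.** The Sample size section gives an average of 150 children at about 35 sites: 150 x 35 = 5,250, as stated. The 150 is used below. The article gives no figure for the share without a measured baseline, overall or by site.

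**Mechanism.** Take creatinine as inversely proportional to clearance. If true baseline clearance is B, the computed ratio is the true ratio x 120/B. A nominal doubling then needs a true rise of 2 x B/120:

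| B | 90 | 100 | 110 | 120 | 140 |
|---|---|---|---|---|---|
| True rise needed | 1.50 | 1.67 | 1.83 | 2.00 | 2.33 |

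Staging is too easy below 120 and too hard above it.

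**Assumptions (not in the documents).**
- Stage 2-3 by creatinine means a ratio of 2 or more.
- 12% of children are truly at that level at both sites, with or without a measured baseline.
- The true ratio is lognormal with SD 0.45 on the log scale.
- Measured baselines are unbiased.
- All children without a measured baseline have the same B.
- Site A has 20% measured baselines and site B has 70%.

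**Formulas.** The normal quantile for 12% is 1.175, so the log-mean is ln 2 - 1.175 x 0.45 = 0.164. Among children without a measured baseline, the proportion staged 2-3 is q = 1 - Phi[(ln(2B/120) - 0.164)/0.45].

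- Site A rate = 0.20 x 12% + 0.80q
- Site B rate = 0.70 x 12% + 0.30q
- Gap = 0.50 x (q - 12%)
- SE of the gap = sqrt[pA(1 - pA)/150 + pB(1 - pB)/150]

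| B | q | Site A | Site B | Gap (points) | SE of gap (points) |
|---|---|---|---|---|---|
| 90 | 29.6% | 26.1% | 17.3% | +8.8 | 4.7 |
| 100 | 22.1% | 20.1% | 15.0% | +5.0 | 4.4 |
| 110 | 16.3% | 15.5% | 13.3% | +2.2 | 4.1 |
| 120 | 12.0% | 12.0% | 12.0% | 0 | 3.8 |
| 140 | 6.5% | 7.6% | 10.3% | -2.8 | 3.3 |

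At B = 100 the gap is 5.0/4.4 = 1.15 standard errors, about a 21% chance of two-sided p<0.05. At 110 it is about 0.5 standard errors (8%). At 100 the gap runs from 3.6 to 6.8 points as the SD goes from 0.60 to 0.35.

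**Other inputs.** A separate simulation took 15% truly severe, SD 0.4, a 20% coefficient of variation in B, and 20% against 80% of children without a measured baseline. The gaps were +14.3 points at a median B of 90, +9.1 at 100, +1.6 at 120 and -2.9 at 140. Over all settings run, with true rates of 10% to 20% and SD 0.4 or 0.5, gaps ran from about -4 to +15 points. Because the inputs differ, this shows how much the size depends on them. It does not confirm the table.

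**Effect of standardising.** At B = 100, weighting both sites to a common 45% measured share gives 0.45 x 12% + 0.55 x 22.1% = 17.5% at each, and the gap disappears. This works because the model gives both sites the same true clearance.

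**The case against.** **The size is unknown.** The article gives neither baseline shares by site nor true clearances. If true clearance averages 120, the gap is 0 in the table and 1.6 points in the simulation. If all sites have the same mix and the same true clearance, there is none. This stands: a reader might infer from the table that the site comparison is biased by some five points, and the documents do not support that.

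**Noise is larger than it looks.** The yardstick for a two-site gap is the standard error of the difference, about 3 to 5 points, and not that of one site. This also stands. Most gaps in the table would not reach significance for a single pair of sites.

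**Urine output.** The outcome section says: "AKI is defined as KDIGO stage 2 or 3 AKI by creatinine and/or urine output criteria on Day 3 or later". Children who qualify by urine output count whatever their baseline. This shrinks the gaps without removing them.

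**The link to KDIGO staging is inferred.** This is true, but the article offers no other baseline for the creatinine stage.

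**It is disclosed, descriptive, and a matter for the analysis plan.** The assumption is disclosed, but its effect on comparing sites is not. The rates are descriptive and no ranking or test of sites is fixed. Even so, the article itself states both the two-rule baseline and the purpose of finding hot spots. The point concerns that stated comparison and not a missing detail.

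**Children with prior creatinines probably differ clinically.** This is likely. It weakens the equal-risk assumption, and it means that baseline source may partly mark real case mix.

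**Conclusion.** The point holds in kind. Followed as written, the site comparison mixes disease with the source of the baseline, and nothing else in the article separates them. Two conditions are needed: the share of measured baselines differs between sites, and the assumed 120 is off on average in the children to whom it is applied. The distortion can go either way. Under the assumptions above it runs from -2.8 to +8.8 points for true clearances of 140 down to 90, and is 0 at 120.

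A reader might go further in two directions that the documents do not support. One is that assuming 120 is wrong for staging in general; the point concerns only the comparison between sites. The other is that one rule for all children, 120 throughout, would make sites comparable. The exclusion criteria remove chronic kidney disease only below an eGFR of 15, so children with known reduced function are eligible. A stable child at eGFR 60 would get a ratio of 120/60 = 2 with no acute injury, and sites with more chronic kidney disease would become false hot spots.

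The change is worth making because it costs little and can alter which sites are called hot spots.

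**What to change.** Keep the main staging as it is. For the site comparison, add to the Analysis section:

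1. Report each site's share of children with a measured baseline.
2. Give site rates separately by baseline source.
3. Standardise site rates to the cohort-wide share, for example with a multilevel model that has baseline source and case mix as covariates, and show the adjusted rates beside the crude ones.
4. Repeat the comparison with the assumed clearance varied (for example over the 90 to 140 used above) only in children without a measured baseline.
5. Call a site a hot spot only if it still stands out in these analyses.

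Measured baselines should not be overwritten with 120.

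**Cost.** A few sentences, one table column and a re-analysis of data already collected. Enrolment, data collection and main staging do not change.

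**Downsides.** Strata within sites are small: 20% of 150 is 30 children, with a standard error of sqrt(0.12 x 0.88/30) = 5.9 points at a 12% rate. Baseline source may carry real case-mix differences, so adjustment can remove some true signal; hence crude and adjusted rates together. Standardising also does not correct true clearance that differs between sites among children without a baseline, which is why the sensitivity analysis is needed as well.
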